## Objectives

### Primary research questions and hypotheses

The primary objective of the current project is to investigate several questions of personalized psychotherapy research with two personalized feedback intervention groups (IG1: Feedback; IG2: Feedback plus CSTs (including personalized predictions before the start of the treatment and adaptation tools during treatment) and one control group (CG) with repeated measurements. As such, this is the first study that prospectively tests the effects of personalized treatment recommendations and adaptation tools. Moreover, it adds to previous feedback research a stricter design by investigating another repeated measurement CG as well as a stricter control of treatment integrity. It also includes a structured clinical interview (SCID) and controls for comorbidity (within depression and anxiety disorders). Furthermore, a severely impaired patient sample is studied and an international outcome instrument is used. This study also investigates the above described moderators (attitudes towards, use of the feedback system, diagnoses) and mediators (therapists’ awareness of negative change and treatment length) in a comprehensive model and in one study.

Therefore, the study allows for testing the following hypotheses:Main hypotheses:H1: *NOT patients in the feedback condition (IG1) show on average better treatment outcomes than NOT patients in the CG.*
H2: *NOT patients in the IG2 (+personalized prediction and adaptation tools) show on average better treatment outcomes than NOT patients of the IG1 (no tools but psychometric feedback).*

Secondary hypotheses concerning moderators and mediators (see also Fig. 1):H3: *The positive impact of feedback for NOT patients is* moderated *through the usage of the feedback system and/or the attitudes of the therapist towards feedback.*

*H3a: The more frequently and the longer feedback is used, the more aware are therapists for negative change.*

*H3b: The more positive the therapists’ attitudes towards feedback, the more aware are therapists for negative change.*

*H3c: The effects of feedback on patient outcomes do not differ between diagnostic groups (depression and anxiety).*

H4: *The positive impact of feedback for NOT patients is* mediated *through therapists’ awareness of negative change as well as treatment length.*

*H4a: The positive impact of feedback for NOT patients is mediated by the therapists’ awareness of negative developments of their patients.*

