**Fig. 1 Fig1:**
[figure not shown]
The mediating and moderating role of variables in the effect of feedback on treatment outcome (path c)

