Three moderators and two mediators of the feedback effect will be investigated in hypotheses 3 and 4 (see also Fig. 1): Moderators: therapists’ attitudes towards feedback, feedback usage and diagnoses; Mediators: Therapists’ awareness for negative developments and treatment length. In order to control for therapist effects, therapists will be modelled as random effects at level two.

Therefore, *Optimal Design Software for Multilevel and Longitudinal Research* (Version 3.01; [50]) was used to determine the minimal effect that can be detected with sufficient power, given the sample size calculation above. Assuming a therapist effect of 5% and k = 50 therapists delivering the treatments to j = 8 patients each, a small effect (d = .2) can be detected with sufficient power (1-β = .8). Thus, given the sample size calculated for the primary hypotheses, the secondary analyses can be conducted with sufficient power using multi-level models (e.g., [51]). Ensuring the stability of the results, all analyses will be checked with Mplus software (e.g., [52]).

Additional Monte Carlo simulations with Mplus (Version 7; [52]) were run to specifically test the mediation models from hypotheses 3 and 4. Assuming again small effects for the direct associations, 10,000 datasets have been simulated with the actual sample size of the study sample. These simulations revealed a sufficient power of 1-β = .874. Thus, given the sample size calculated for the primary hypotheses, the mediation analyses can also be conducted with sufficient statistical power to detect indirect mediation effects adjusting for above described control variables.

Furthermore, the analyses will be controlled for the following potential influencing factors: comorbidity (number of additional diagnoses, additional personality disorders), initial impairment, clinical experience as well as experience with the feedback system.

Finally, the data of the project will have a hierarchical data structure because patients will be nested within therapists. Two-level hierarchical models will be applied to the data to correct for therapist influences [51].

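### H3 asserts that usage and therapist attitude moderate the feedback effect, but H3a and H3b state only associations with therapist awareness

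*Protocol article*

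**What the plan says.** Under Objectives, H3 states that the positive impact of feedback for NOT patients is moderated "through the usage of the feedback system and/or the attitudes of the therapist towards feedback". Two sub-hypotheses carry this for usage and attitude: "H3a: The more frequently and the longer feedback is used, the more aware are therapists for negative change" and "H3b: The more positive the therapists’ attitudes towards feedback, the more aware are therapists for negative change". The third, H3c, concerns diagnosis and is worded as a statement about effects of feedback on patient outcome across diagnostic groups.

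Awareness has another role in H4: "H4a: The positive impact of feedback for NOT patients is mediated by the therapists’ awareness of negative developments of their patients". The caption of Fig. 1 places the moderators and mediators on the effect of feedback on treatment outcome, labelled path c.

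The section on sample size and data analyses lists, as moderators of the feedback effect, "Moderators: therapists’ attitudes towards feedback, feedback usage and diagnoses". It then gives a generic multilevel power statement (d = .2, 50 therapists with 8 patients each, therapist effect 5%). It continues: "Additional Monte Carlo simulations with Mplus (Version 7; [52]) were run to specifically test the mediation models from hypotheses 3 and 4". The power reported from those simulations is .874, for indirect mediation effects.

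**The concern.** Moderation means that the size of the feedback effect changes with the level of the moderator, which is an interaction with treatment condition. H3a and H3b state main-effect associations with a variable that the protocol elsewhere treats as a mediator. The parent claim and the statements meant to carry it therefore have different null hypotheses.

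An attitude-awareness association could be reported as evidence that feedback works better with some therapists when nothing is moderated. A therapist attitude that really alters the benefit of feedback, for example by prompting action on the signal, would not show in H3b if awareness is unchanged. Moderators and mediators are a headline aim of the study, and the Background faults earlier work for lacking specific power analyses of them.

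**Working it through.** **The two hypotheses side by side.** Let F be condition (feedback or control) and A therapist attitude.

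- H3: outcome = b0 + bF·F + bA·A + bFA·F·A. The null is bFA = 0.
- H3b: awareness = g0 + gF·F + gA·A. The null is gA = 0.

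If gA is non-zero and equal in both conditions, H3b is true while bFA can be zero. If bFA is non-zero and gA is zero, H3 is true and H3b false. Neither implies the other. If the moderators are meant to act on the path from feedback to awareness, the term needed is F·A in the awareness model. H3b does not contain that either.

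**Can H3b hold in control patients?** Awareness is the agreement of therapist GAF with patient HSCL ratings. Table 1 schedules both at every session without restriction by group, so awareness exists in the control group (CG). Portal usage does not, because CG therapists receive no computer-based feedback on those patients. H3a can therefore only describe a dose-response among feedback patients.

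**The plan's own power figures.** The .874 cannot be recomputed, since its path values are described only as small. For d = .2 with 400 patients and a 5% therapist effect:

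- randomisation within therapist: SE = √(4 × .95/400) = .0975; power = Φ(.2/.0975 − 1.96) = .54;
- randomisation by therapist: SE = √(4 × (.05 + .95/8)/50) = .116; power = .41.

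So the stated .8 does not reproduce without an unstated covariate gain. That is a separate matter. What counts here is that the statement is not identified as a calculation for an interaction.

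**Illustration with assumed slopes.** Two settings, both with a therapist effect of 5%:

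- A: 50 therapists, 160 NOT patients (40% of 400), 20% of them in CG.
- B: randomised groups only; 34 CG and 68 IG2 NOT patients (40% of 85 and 169), total 102; about 32 therapists (254/8).

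Attitude raises awareness by b SD per SD, equally in both conditions, and nothing is moderated. With n NOT patients per therapist and K therapists, SE = √((.05 + .95/n)/K).

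- A: n = 3.2, SE = .083.
- B: n = 3.19, SE = .104.

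The chance that H3b is confirmed is Φ(b/SE − 1.96):

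| b (assumed) | A: formula | A: simulated | B: formula | B: simulated |
|---|---|---|---|---|
| .1 | .22 | .227 | .16 | .146 |
| .2 | .67 | .633 | .48 | .449 |
| .3 | .95 | .932 | .82 | .759 |

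In setting A the condition-by-attitude interaction on outcome rejects in .049 to .061 of the same trials.

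Reversed case: attitude changes the feedback effect on outcome by .5 SD per SD and is unrelated to awareness. H3b then rejects in .047 (A) and .049 (B); the interaction test rejects in .659 and .614.

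**Does leaving out CG help?** Take only the 68 IG2 patients of setting B: n = 68/32 = 2.125, SE = √((.05 + .95/2.125)/32) = .125. H3b is confirmed with probability .13, .36 and .67 for the three slopes. Fewer patients lower the rate, but there is now no comparison at all from which moderation could be inferred.

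**What an interaction would need.** With IG2 share p among N NOT patients, SE ≈ √(.95/(N·p(1−p))). For N = 102 and p = 2/3, SE = √(.95/22.67) = .205. The change detectable with 80% power is 2.80 × .205 = .57 SD in the feedback effect per SD of attitude. For the 27 + 54 = 81 NOT patients without the drop-out buffer, SE = √(.95/18) = .230, giving .64.

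**The case against.** The strongest reply is that the wording is loose but the intention is clear. H3 itself says moderated, the analysis section names the three moderators of the feedback effect, and exact model terms belong to a full analysis plan. Fig. 1, which is not reproduced in the text at hand, may place the moderators on the feedback-to-awareness path. H3 and H4 would then form a moderated-mediation model, and the shared mediation simulation would make sense. The simulated percentages follow from slopes that were put in.

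Much of this stands:

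- A reader might infer that a significant H3b would lead to H3 being declared supported. The protocol states no such rule.
- A reader might take the percentages as this trial's risk. They are not: the slopes, the .5 SD moderation and the 32 therapists are assumptions, and the table pools CG patients, which the protocol does not prescribe.
- A reader might say that H3 has no power statement. The generic d = .2 statement covers the secondary analyses.
- Insisting on outcome alone would override a moderated-mediation model if that is what Fig. 1 shows.

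The objection does not remove the mismatch. Either placement of the moderators needs a condition-by-attitude interaction, and neither H3a nor H3b states one. H3c shows that effect modification could be worded properly under the same parent. This is a hypothesis wrongly stated, not detail left to another document.

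**Conclusion.** The point holds as a mismatch between H3 and its sub-hypotheses on usage and attitude, and in the description of H3 as a mediation model. A result on H3b, in either direction, does not answer H3. The conclusion rests on the text and needs no numerical assumption. Any non-zero attitude-awareness slope shared by both conditions can confirm H3b without moderation. The frequency cannot be estimated from the protocol; the 15% to 93% range only shows how strongly it depends on the slope and sample assumed. The matter is secondary, but it should be corrected before the moderator results are interpreted.

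**What to change.** - **H3b.** Restate it as a condition-by-attitude interaction in the planned two-level model for NOT patients. Test it on patient outcome, the effect named in H3 and in the Fig. 1 caption. If moderated mediation is intended, test it on awareness as well.
- **Contrast.** Use randomised CG versus IG2, which can be estimated within therapist because each therapist treats patients in both groups. Note that it covers feedback together with the recommendation and support tools. IG1 versus CG, closer to feedback alone, would be a non-randomised supplement, provided attitude is available for the archival therapists.
- **H3a.** Restate it as a dose-response association within feedback patients, not as moderation of feedback versus none.
- **Descriptive result.** Report the attitude-awareness association as descriptive.
- **Power text.** Limit .874 to the indirect effects, stop calling H3 a mediation model, and state the power of the interaction separately from the d = .2 statement.

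The cost is rewording, one interaction term (two if awareness is included) and one power calculation. No new data are needed, since attitude is recorded when each therapist starts in the project. The downside is a less favourable stated power for H3.

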**Methods/design:**

The research project investigates in a randomized controlled trial the effectiveness as well as moderating and mediating factors of psychometric feedback to therapists. In the intended study a total of 423 patients, who applied for a cognitive-behavioral therapy at the psychotherapy clinic of the University Trier and suffer from a depressive and/or an anxiety disorder (SCID interviews), will be included. The patients will be randomly assigned either to one therapist as well as to one of two intervention groups (CG, IG2). An additional intervention group (IG1) will be generated from an existing archival data set via propensity score matching. Patients of the control group (CG; *n* = 85) will be monitored concerning psychological impairment but therapists will not be provided with any feedback about the patients assessments. In both intervention groups (IG1: *n* = 169; IG2: *n* = 169) the therapists are provided with feedback about the patients self-evaluation in a computerized feedback portal. Therapists of the IG2 will additionally be provided with clinical support tools, which will be developed in this project, on the basis of existing systems. Therapists will also be provided with a personalized treatment recommendation based on similar patients (Nearest Neighbors) at the beginning of treatment. Besides the general effectiveness of feedback and the clinical support tools for negatively developing patients, further mediating and moderating variables on this feedback effect should be examined: treatment length, frequency of feedback use, therapist effects, therapist’s experience, attitude towards feedback as well as congruence of therapist’s and patient’s evaluation concerning the progress. Additional procedures will be implemented to assess treatment adherence as well as the reliability of diagnosis and to include it into the analyses.

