### Sample size calculation and data analyses

Since the two main hypotheses are based on pairwise comparisons of the NOT patients, the sample size calculation was done so that the size of these comparisons have sufficient power (1-β = .8). Power analyses for the main hypotheses have been conducted with GPower 3.1 [47]. Hypothesis 1 postulates a superior treatment outcome for NOT patients in the IG1 compared to the CG. The average effect for feedback in NOT patients compared to treatment as usual found in the literature is between *r =* .25 [17]. To find this effect in a two-way repeated measures ANOVA with (feedback yes/no) and assessment time (pre/post) with a power of at least 80%, an a priori significance level of .05, and a correlation between assessments of .4, the sample has to include at least *N* = 38 NOT patients in total (IG1 and CG). The incremental effect for feedback with CSTs in comparison with feedback without CSTs was *d =* .31 [48]. We therefore assume a small incremental effect (*d =* .30) for the use of CST in this project. To find this effect in a two-way ANOVA with (feedback yes/no) and assessment time (pre/post) with a power of at least 80%, an a priori significance level of .05, and a correlation between assessments of .4, the total sample has to include *N* = 108 NOT patients in total (IG 1 and IG 2). To make sure, that treatment groups and CST are more comparable with respect to the number of patients, we added for the sample size calculation in the CG half of the NOT patients in IG1/IG2, resulting in at least 27 NOT patients for the CG.

In a previous study the proportion of patients who received at least one alarm signal within the first 8 sessions was approximately 49% [49]. Also, Simon et al. found that 56% of the patients were NOT and therefore received an alarm signal [22]. For our sample size calculation we used a more conservative estimate of 40% of NOT patients, which results in a total sample size of *N* = 338 (CG = 68, IG = 135, IG2 = 135). In order to control for drop-out, we added a puffer of 25% to the required sample size to make sure the power analysis is valid. The described procedure above, results in final sample sizes for each group shown in Table 2.

**Table 2 Tab2:** Intended recruitment and sample size of treatment groups

Treatment	Sample size
Intervention group 1	169
Intervention group 2	169
Control group	85

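### H3c puts forward equal feedback effects in depression and anxiety as a testable hypothesis, but the stated power is for detecting an overall effect and the design says little about the diagnosis-by-group interaction

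*Protocol article*

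**What the plan says.** In the protocol article, the section on primary research questions and hypotheses says that the study permits tests of a list of hypotheses. H3c stands among the secondary ones: "The effects of feedback on patient outcomes do not differ between diagnostic groups (depression and anxiety"). It is a prediction of no difference, and no margin is attached.

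The section on sample size and data analyses treats diagnosis as one of three moderators: "Moderators: therapists’ attitudes towards feedback, feedback usage and diagnoses". The main sample size is built on NOT patients: "Since the two main hypotheses are based on pairwise comparisons of the NOT patients". It gives 108 NOT patients in IG1 and IG2 together and at least 27 in the control group (CG), using "an a priori significance level of .05, and a correlation between assessments of .4". At an assumed 40% of NOT patients this becomes 338 patients (68 / 135 / 135), and 423 (85 / 169 / 169) after a 25% addition for drop-out.

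For the secondary analyses the section reports that d = .2 is detectable with power .8, given a therapist effect of 5% and 50 therapists with 8 patients each. It concludes that these analyses have sufficient power. It also reports Monte Carlo simulations for the mediation models, with power .874.

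On eligibility, the abstract says patients "suffer from a depressive and/or an anxiety disorder (SCID interviews"), and the inclusion criteria ask for at least one such disorder. A patient may therefore have both.

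**The concern.** A stated hypothesis and a stated power property do not fit together. Power of .8 to detect an effect says how often a real effect would be found. It says nothing about how well the trial could show that two effects are equal. For a no-difference hypothesis the relevant quantity is the width of the confidence interval for the difference, and the article gives neither that nor a margin to compare it with.

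The calculation is also for a different quantity. It concerns an overall effect, whereas H3c concerns a difference between two treatment effects, which is estimated much less precisely.

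At stake is how the result is read. The Background says that diagnostic group has not been studied as a moderator of feedback, so a report of equal effects could be cited as first evidence. With wide intervals, such a report would reflect lack of information and not similarity.

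**Working it through.** **Inputs from the protocol article (sample size section).** Pre/post correlation .4; NOT patients 108 feedback v 27 CG; evaluable patients 135 + 135 = 270 feedback v 68 CG; recruited patients 169 + 169 = 338 feedback v 85 CG; H1 effect r = .25; H2 effect d = .30; secondary power calculation with 50 × 8 patients, therapist effect 5%, d = .2.

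**Assumptions made here.** Half the patients in each diagnostic group (70:30 as sensitivity); baseline-adjusted analysis with residual variance 1 − .4² = .84 (change-score variance 2(1 − .4) = 1.2 as sensitivity); IG1 and IG2 pooled as feedback; no allowance for therapist variation in the effect or for the matching of IG1, both of which would widen the intervals.

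**1. The plan's own figure.** If treatment varies within therapist, the noncentrality is 50 × .2² / (4 × .95 / 8) = 2 / .475 = 4.21, which gives power .52. If it varies between therapists, it is 50 × .2² / [4 × (.05 + .95/8)] = 2 / .675 = 2.96, power .39. A one-sided test gives .66, and baseline adjustment gives .59. The stated .8 is not reproduced from the listed inputs, but the article may not list every input given to the software. This is a separate matter and the point does not rest on it.

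**2. The plan's figure at face value.** With equal diagnosis groups, the variance of the interaction is 4v(1/n₁ + 1/n₀), against v(1/n₁ + 1/n₀) for the overall effect, so the standard error doubles. If d = .2 were detectable as an overall effect, the detectable interaction in the same 400 patients would be 2 × .2 = .40 SD.

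**3. Precision for H3c.** SE = √[4 × .84 × (1/n_feedback + 1/n_CG)]; half-width = 1.96 × SE.

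| Sample | SE | 95% half-width | Half-width at 70:30 |
|---|---|---|---|
| NOT, 108 v 27 | √(3.36 × .04630) = .394 | .77 | .84 |
| All evaluable, 270 v 68 | √(3.36 × .01841) = .249 | .49 | .53 |
| All recruited, 338 v 85 | √(3.36 × .01472) = .222 | .44 | .48 |

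With change-score variance and a 50:50 split, the half-widths are .92, .58 and .52.

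**4. Power for the interaction (two-sided .05).** The H1 effect is d = 2 × .25 / √(1 − .25²) = .52. An interaction of that size means a .52 SD effect in one diagnosis and none in the other.

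| Sample | Power at .52 SD | Power at .30 SD |
|---|---|---|
| NOT, 108 v 27 | .26 | .12 |
| All evaluable, 270 v 68 | .55 | .23 |
| All recruited, 338 v 85 | .64 | .27 |

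In NOT patients such a contrast would be missed about 74% of the time (1 − .26). In all evaluable patients it would be missed about 45% of the time (1 − .55), if the effect there were as large as the one the article takes for NOT patients.

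**5. What a similarity claim would need.** The article gives no margin, so .30 and .50 SD are used only as illustrations. At .30 SD every half-width in step 3 exceeds the margin, so the interval could never lie inside it. At .50 SD, with two one-sided tests at .05 and a true difference of zero (50:50 split, variance .84), power is 0% in NOT patients, about 29% in all evaluable and 45% in all recruited. For 80% power at .30 SD, about 1,280 patients would be needed in four equal cells, or about 2,000 at the planned 1:4 split of control to feedback.

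**The case against.** The strongest reply is that the article never says how H3c will be judged. A reader might infer that a non-significant interaction will be taken as confirmation, but no sentence says so, and a criterion could stand in an analysis plan that is not shown. That is right, and the absence of a margin is not itself the point. What stands is what the article does say: H3c is testable and the secondary analyses have sufficient power. No other criterion is given, and no planned sample could meet a margin of .30 SD.

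A reader might also infer that the depression–anxiety contrast is undefined for a large part of the sample. The article does not support this. It gives no comorbidity rate, it says that comorbidity is controlled, and its adjustment for the number of additional diagnoses suggests an index diagnosis by which patients could be grouped. What remains is that both disorders can occur in one patient and the grouping is not stated.

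It is tempting to quote only the NOT figures. The parent hypothesis H3 concerns NOT patients, but H3c does not repeat that limit, so both populations are shown. Nor is .30 SD a relevance threshold of the plan: it is the assumed H2 increment ("We therefore assume a small incremental effect"), and the secondary calculation uses .2. The simulation power of .874 is for mediation and does not bear on H3c. Finally, H3c is a sub-hypothesis of a secondary hypothesis; calling it a headline result would overstate it.

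**Conclusion.** The point holds in this limited form. H3c states a null as a hypothesis to be tested, and the power statement that covers it is of the wrong kind and for the wrong quantity. The interaction would be estimated to about ±.77 SD in NOT patients, wider than the whole .52 SD effect assumed for H1, and to about ±.49 SD in all evaluable patients (±.44 SD if all 423 are analysed). In NOT patients a non-significant test would be the usual result even if feedback had its full assumed effect in one diagnosis and none in the other. In all patients the test is better but still far from decisive.

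The figures rest on an assumed 50:50 diagnosis split, residual variance .84 and pooled feedback groups. The unequal split and the change-score analysis that were tried both give wider intervals. That the sponsor will read non-significance as equality is a risk left open by the text, not something the text says. The change is worth making because it costs almost nothing; it does not touch the main hypotheses.

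**What to change.** Restate H3c as estimation: report the diagnosis-by-group interaction with its 95% confidence interval, and draw no conclusion of equal effects from a non-significant test. Claim similarity only if the interval lies within a margin that the sponsor justifies in advance; otherwise report the result as inconclusive. Say whether H3c is analysed in NOT patients or in all patients. State in the sample size section that the sufficient-power claim does not apply to H3c.

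Because eligibility allows both disorders, either model depression (yes/no) and anxiety (yes/no) as two indicators, or group patients by index diagnosis, so that comorbid patients are kept.

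The cost is a change of wording and no extra patients. The downside is an open admission that the trial will probably be inconclusive on H3c.
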